### Sample size

The intervention group consists of all AGR participants, receiving the AGR in Mecklenburg-Vorpommern during the years 2009–2013. This will comprise approximately 700 patients. Controls will be chosen from a pool of around 250.000 members of the AOK Nordost aged 70 years and older. Approximately 2800 controls will be selected from the pool.

### Outcome measures and data collection

Claims data will comprise the billing periods from 01.01.2008 until 31.12.2014, thus ensuring a minimal observation period of 12 months prior and after the index billing period. All variables are provided for each billing period during the observation period.

The primary outcomes are ‘*progression of nursing care level*’, ‘*admission to nursing home*’ and ‘*incident fractures*’.

Four nursing care levels (0–3) are defined by the German social code XI (SGB XI). The nursing care level needs to be approved by the Medical Review Board of the statutory health insurances (MDK) in a standardised procedure. The definition for nursing care level is described in Table 4 [13]. Elderly who do not reach the requirements for nursing care level I, but need help for daily living (SGB XI § 45a) receive care for their needs. This is referred to as nursing care level 0 [13].

**Table 4 Tab4:** Definitions of the nursing care levels [13]

	Requirements	
Nursing care level	total daily help (including help in household)	personal help (included in total daily help)
1	minimum 1,5 h	>45 min
2	minimum 3 h	≥2 h, 3 times a day
3	minimum 5 h	≥4 h permanent help

The outcomes ‘*admission to nursing home*’ and ‘*incident fractures*’ are both coded as binary variables, stating whether the patients experienced the event after the index billing period or not.

Secondary outcome variables are ‘any *hospital admission*’ (yes/no), ‘*days spent in the hospital*’, ‘*ambulatory care sensitive hospital admissions*’ (yes/no) and ‘*total health care costs from the statutory health insurance perspective*’ during the entire follow-up period and during each billing period in the follow-up period. Ambulatory care sensitive hospital admissions are defined as potentially preventable hospital admissions by interventions in primary care and are displayed in Table 5. Conditions were chosen from two studies [14, 15].

**Table 5 Tab5:** Ambulatory care sensitive conditions used to define hospital admissions to be prevented by AGR (according to [14, 15])

Ambulatory care sensitive conditions	ICD-10 code
Ischaemic heart diseases	I25.0, I25.1, I25.5, I25.6, I25.8, I25.9
Heart failure	I50
Other diseases of the circulatory system	I05, I06, I08.0, I49.8, I49.9, I67.2, I67.4, I70, I73, I78, I80.0, I80.80, I83, I86, I87, I95, R00.0, R00.2
Bronchitis & COPD	J20, J21, J40-J44, J47
Mental and behavioural disorders due to use of alcohol or opioids	F10, F11
Back pain [dorsopathies]	M42, M47, M53, M54
Hypertension	I10 - I15
Gastroenteritis and other diseases of intestines	K52.2, K52.8, K52.9, K57, K58, K59.0
Intestinal infectious diseases	A01, A02, A04, A05, A07-A09
Influenza and pneumonia	J10, J11, J13, J14, J15.3, J15.4, J15.7, J15.8, J15.9, J16.8, J18.0, J18.1, J18.8, J18.9
Ear nose throat infections	H66, H67, J01-J04, J06, J31, J32, J35
Depressive disorders	F32, F33
Diabetes mellitus	E10.2-E10.6, E10.8, E10.9, E11, E13.6, E13.7, E13.9, E14, E16.2
Gonarthrosis [arthrosis of knee]	M17.0, M17.1, M17.4, M17.5, M17.9
Soft tissue disorders	G56.0, M67.4, M71.3, M75-M77, M79
Other avoidable mental and behavioural disorders	F40, F41, F43, F45, F50.0, F50.2, F60
Diseases of the eye	H25, H40
Diseases of urinary system	N30, N34, N39.0
Sleep disorders	G47
Diseases of the skin and subcutaneous tissue	A46, L01, L02, L04, L08.0, L08.8, L08.9, L60.0, L72.1, L98.0
Thyroid disorder	E03 - E05, E89.0
Metabolic disorders	E86, E87.6
Melanoma and other malignant neoplasms of skin	C43, C44
Gastritis and duodenitis	K21, K29.7, K29.9, K30, K31
Migraine and headache syndromes	G43, G44.0, G44.1, G44.3, G44.4, G44.8, R51
Malnutrition & nutritional deficiencies	E40 - 64, R63.6, D50, D51-D52, D53.1, D56
Alcoholic liver disease	K70
Dental diseases	K02, K04-K06, K08, K12, K13
Inflammatory diseases of female pelvic organs and disorders of female genital tract	N70-N72, N75, N76, N84.1, N86, N87
Dementia	F01, F03
Diseases of male genital organs	N41, N45, N48.4
Asthma	J45
Other polyneuropathies	G62
Avoidable infectious and parasitic diseases	A15.3, A15.4, A15.9, A16.2, A16.3, A16.5, A16.8, A16.9, A34 - A37, A50-A58, A63, A64, A80, B05 - B07, B15, B16.1, B16.9, B17, B18.0, B18.1, B20 - B24, B26, B34.9, B51 - B54, B77, B86
Convulsions, not elsewhere classified	R56
Decubitus ulcer and pressure area	L89
Obesity	E66
Rare diseases with <5000 cases each	F80, R63.0, R63.3, R63.8, Z73
Cellulitis	L03, L04, L08.0, L08.8, L08.9, L88, L98.0, I891, L010, L011, L020 - L024, L028, L029
Angina	I20, I24.0, I24.8, I24.9, I25, R072, R073, R074, Z034, Z035
Convulsions and epilepsy	G25.3, G40, G41, O15, R56, R568
Dehydration and infections	A02, A04, A09, A05.9, A07.2, A08.0, A08.1, A08.3, A08.4, A08.5, E86, K52.0, K52.1, K52.2, K52.8, K52.9
Gangrene	R02
Iron-deficiency anaemia	D46.0, D46.1, D46.3, D46.4, D50.1, D50.8, D50.9, D51.0–D51.3, D51.8, D52.0, D52.1, D52.8, D52.9, D53.1, D57.1, D58.0, D58.1, D59.0 – D59.2, D59.9, D60.1, D60.8, D60.9, D61.0, D61.1, D64.0 - D64.4, D64.8
Pelvic inflammatory disease	N70, N73, N74
Perforated/bleeding ulcer	K20, K21.0, K21.9, K22.1, K22.6, K25.0 – K25.2, K25.4 – K25.6, K25.9, K26.0 – K26.2, K26.4 – K26.6, K27,K28.0 – 28.2, K28.4 – K28.6, K92.0, K92.1, K92.2, L97
Pyelonephritis	N10, N11, N12, N13.6, N15.9, N30.0, N30.8, N30.9, N39.0,
Atrial fibrillation and flutter	I47.1, I47.9, I49.5, I49.8, I49.9, R00.0, R00.2, R00.8
Constipation	K59.0
Deliberate self-harm	S16
Dyspepsia and other stomach function disorders	K21, K30
Hypokalaemia	E87.6
Neuroses	E10, E13.6 – E13.9, E14.9
Tuberculosis	A15, A16, A17, A18, A19
Schizophrenia	F20, F21, F23.2, F25
Stroke	I61, I62, I63, I64, I66, I67.2, I69.8, R47.0

‘*Total health care costs*’ comprises expenditures for hospitalisation, remedies and medical aids, ambulatory costs, and medication. The variables concerning costs refer to costs excluding out-of-pocket spending except for remedies and medical aids where the available data does not allow for any separate analysis of out-of-pocket spending.

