Preventive ambulatory geriatric rehabilitation (AGR [*Ambulante Geriatrische Komplexbehandlung*]) was introduced in 2008 within the legal frame (§ 140 Book V of the social code) of selective contracts for integrated care. Therefore it is only available as a model intervention in some areas for holders of specific statutory health insurances (e.g. AOK Nordost). AGR is not part of regular health care.

It is intended as a community based outpatient intervention to improve patient’s physical function, increase patient’s safety and quality of life as well as to prevent falls and injuries, to avoid and delay hospitalisation, the progression of nursing care level and admission to nursing home.

A systematic review of controlled trials of ambulatory and hospital interventions to improve physical function and maintain independent living in elderly people concluded that they were effective to achieve the goal [1]. This review comprised only one German trial which included geriatric patient post hospital discharge [11]. However, AGR is primarily intended to prevent hospitalisation and not as a post-discharge rehabilitation. The effectiveness of German AGR programs has not been evaluated rigorously yet. Previous studies have relied on uncontrolled study designs [12].

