### Objectives and hypotheses

The aim of our study is to evaluate the effectiveness of AGR regarding patient’s progression to higher nursing care levels, incident fractures, admission to nursing home, hospital admissions as well as health care costs. For this purpose we compare patients receiving AGR with patients receiving care as usual. We will estimate average treatment effects based on a cohort design using propensity score techniques to match cases and controls. The follow-up period will be up to 2 years.

*Our primary hypotheses are*:AGR reduces and delays progression to higher nursing care levels.AGR reduces and delays nursing home admissions.AGR reduces the risk of incident fractures.

*Our secondary hypotheses are*:AGR decreases and delays hospital admissions and reduces the days spent in hospital during follow-up time.AGR decreases and delays ambulatory care sensitive hospital admissions.AGR decreases total health care costs from the statutory health insurance perspective.

On an exploratory basis we will investigate the effect on drug prescriptions.

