## Methods

### Study design

The conduct of a randomised controlled trial to assess the effectiveness of AGR is currently limited due to logistic and ethical reasons. Therefore we will conduct a matched cohort study using claims data. Anonymised data will be provided by the statutory health insurance AOK Nordost which comprises basic demographic data, data on nursing care level, admission to a nursing home, billing data for ambulatory services (EBM position numbers) and for hospital services (DRG-codes/OPS-codes), as well as diagnoses (ICD-10 codes), and all health care costs, including costs for hospitalisation, remedies and aids, ambulatory costs and costs for medication. To balance potential confounders, we will apply a propensity score matching. Controls will be matched patients insured by the AOK Nordost.

The observation period comprises 4 billing periods (each 3 months, corresponding to 1 year) prior to the intervention, the intervention (index) billing period, and up to 8 billing periods post intervention, resulting in a total observation period of up to 13 billing periods. The billing period covering the most days of the intervention will be considered as the index billing period. Participants in the intervention group received a 4 weeks AGR in between the years 2009 and 2013.

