### Exclusion criteria from the analyses

We aim to quantify treatment effects for typical AGR patients. Therefore, we will exclude participants with rare conditions which are likely to affect the health course beyond the effects which can be reasonably assumed from AGR (e.g. organ transplantation, dialysis, chemotherapy) or participants with extremely high health care costs indicating severe conditions. Prespecified criteria used to exclude AGR participants from our analyses are shown in Table 3. Exclusion criteria for AGR participants also apply to potential controls.

**Table 3 Tab3:** Criteria for the exclusion of AGR participants for study analysis

Exclusion criteria	
- Age <70 or >95 years in the intervention billing period Prior to the intervention billing period: - nursing care >2 - <360 insured days in the four previous billing periods - living in a nursing home - hospital costs without out of pocket spending at the last billing period >33.000 € - hospital costs without out of pocket spending during the four last billing periods ≥44.000 € - ambulatory costs during the last billing period ≥2.200 € - ambulatory costs during the four last billing periods ∑ ≥5.500€ - remedy costs without out of pocket spending during the four previous billing periods ≥2.200 € - costs of aid without out of pocket spending during the four previous billing periods ≥4.000 € - drug costs without out of pocket spending during the four previous billing periods AGR ≥11.000 € - total health care costs without out of pocket spending during the four previous billing periods ≥44.000 € - diagnosed AIDS/HIV in the four previous billing periods - chemotherapy in the four previous billing periods - organ transplantation during the four previous billing periods - dialysis during the four previous billing periods	

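### The test of total insurer cost uses a follow-up window that leaves out nearly all of the insurer's payment for AGR, so the cost difference favours AGR by about the programme price

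*Protocol article*

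**What the plan says.** All references are to the protocol article.

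- **Hypothesis** (Objectives and hypotheses): "AGR decreases total health care costs from the statutory health insurance perspective". Nothing restricts it to costs arising after the programme.
- **Components** (Outcome measures and data collection): total cost "comprises expenditures for hospitalisation, remedies and medical aids, ambulatory costs, and medication". Neither AGR nor a selective-contract payment is named.
- **Window** (same section): the secondary outcomes are taken "during the entire follow-up period and during each billing period in the follow-up period".
- **Timeline** (Study design): four quarters of history come first, followed by "the intervention (index) billing period, and up to 8 billing periods post intervention, resulting in a total observation period of up to 13 billing periods". Of these, the index period is the quarter that contains most of the AGR days.
- **Funding and content**: the Background places AGR within "selective contracts for integrated care", outside regular care. The description of the intervention gives about 20 treatment days with several therapy sessions a day, plus meals and daily transport.
- **Out-of-pocket convention**: costs are net of patients' own payments "except for remedies and medical aids where the available data does not allow for any separate analysis of out-of-pocket spending" (Outcome measures and data collection). Table 3 nevertheless excludes on "remedy costs without out of pocket spending during the four previous billing periods ≥2.200" euros, and words its aid and total-cost thresholds in the same way.

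**The concern.** For the payer, the price of the programme is part of the answer to whether the programme lowers total cost. Control patients incur no such payment. If it is left out of the AGR arm, the comparison shifts in one direction only, and neither a larger sample nor better matching removes the shift. A downstream saving smaller than the price would appear as lower total cost although the insurer had spent more overall. The Discussion says the results are meant to inform whether AGR is continued, changed or expanded, so the sign of this contrast matters.

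**Working it through.** **1. Is the index period inside follow-up?** The protocol's own count is 4 prior + 1 index + 8 post = 13 billing periods, which matches the stated total. Follow-up is stated as up to 2 years, and 8 × 3 months = 24 months, so the 8 post-intervention periods use up all of it. The index period lies outside.

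**2. How much of AGR can fall in follow-up?** Suppose the payment were held under ambulatory costs and booked by day of treatment. Assume a 28-day course (the stated 4 weeks) and start days uniform over a 91-day quarter. Only courses that cross the quarter end with at least half their days before it put any days into follow-up:

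- spill-over of 1 to 14 days: 14/91 = 15% of courses
- largest share of one course: 14/28 = 50%
- mean share over all courses: (1 + 2 + … + 14)/(28 × 91) = 105/2,548 = 4.1%

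Quarters of 90 or 92 days give 4.2% and 4.1%. The window alone therefore removes about 96% of the payment. If the four cost headings do not carry the contract payment at all, 100% is missing.

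**3. Effect on the estimate.** Let C be the payment per AGR patient and s the share of it that falls in follow-up.

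- Insurer's full difference = post-programme difference + C
- Planned difference = post-programme difference + sC
- Error = −(1 − s)C, that is −0.96C to −C for s between 0.04 and 0

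Illustration with assumed figures and s = 0: with a downstream saving of EUR 500 and a price of EUR 1,500, the plan reports −500, while the insurer's position is −500 + 1,500 = +1,000.

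**4. Effect on the test.** The stated group sizes are about 700 and 2,800. C and the SD of cost are not in the documents and are assumed here. The approximation is an unadjusted two-sample comparison, two-sided 5%:

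- SE = SD × √(1/700 + 1/2,800), which is EUR 338, 507 and 676 for SD = 8,000, 12,000 and 16,000
- If AGR saves exactly its own price (net effect zero) and s = 0, P(saving declared) = Φ(C/SE − 1.96)

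| Assumed C (EUR) | SD 8,000 | SD 12,000 | SD 16,000 |
|---|---|---|---|
| 1,000 | 0.84 | 0.51 | 0.32 |
| 2,000 | >0.99 | 0.98 | 0.84 |
| 3,000 | >0.99 | >0.99 | 0.99 |
| 4,000 | >0.99 | >0.99 | >0.99 |

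The nominal probability in that direction is 0.025. With s = 0.04 the lowest entry falls only from 0.32 to 0.30.

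**5. Out-of-pocket labels.** Table 3 has three thresholds labelled net of out-of-pocket spending that depend on remedies or aids: remedies (2,200), aids (4,000) and total cost (44,000, which contains both). The outcome section says that this separation is not possible for remedies and aids. The three thresholds cannot be applied as labelled.

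**The case against.** A reader might infer that the outcome can never contain any AGR payment and that exactly the full price is lost. The documents do not go that far. They do not expressly exclude the payment. Study design describes the supplied cost data in open-ended terms, and ambulatory costs could hold the payment for an ambulatory programme. Booking is not described: a course crossing a quarter end would put a small part into follow-up, and booking by a later invoice date could put in more. The component list alone would therefore not settle the matter. The window carries the argument.

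It is also fair to say that post-programme cost is a legitimate quantity and that the window is stated openly. What remains is the mismatch: the hypothesis is worded as total insurer cost without qualification, and the fixed window does not measure that. This is a stated rule, not detail that a condensed article leaves to a fuller document.

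Counting every insurer cost from the start of the index period may look like the natural repair, but it would bring in a new bias. The matching section says that the order of events within a billing period is unknown and that events leading to AGR may lie in the index period. Under scenario b, index-period costs are also matching variables.

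On out-of-pocket spending, a reader might infer that exclusion, matching and outcome all conflict. Table 6 puts no net-of-payment label on remedies and aids, and a matching variable need not share the outcome's definition. The conflict is confined to Table 3.

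**Conclusion.** The point holds in this form: followed as written, the planned comparison leaves out nearly all of what the insurer pays for AGR, and the cost difference favours AGR by about the programme price. The direction follows from the protocol's timeline. The 0.96C to C range assumes booking by treatment day or no booking under the four headings, with uniform start dates. The size in euros cannot be derived because no price is given. The error probabilities rest on assumed prices and SDs and on a simple two-sample approximation.

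Cost is a secondary outcome. The primary outcomes and the hospital outcomes are unaffected. The Table 3 labelling conflict is real but minor, and it has no bearing on the AGR-payment bias.

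**What to change.** 1. Obtain from the insurer the AGR contract payment per patient, with the cost heading and period in which it is booked.
2. For the test of the total-cost hypothesis, add that payment, and nothing else, once to each AGR patient's follow-up cost. First check that it is not already in follow-up ambulatory costs, so that it is not counted twice.
3. Report follow-up-only cost, overall and by billing period, as a separate outcome labelled post-programme cost excluding AGR.
4. Do not add other index-period costs to the main outcome, because they may precede AGR.
5. If the payment is booked in index-period ambulatory or total costs, remove it from the scenario b matching variables. Otherwise AGR patients would be matched partly on having received AGR.
6. Separately, relabel the Table 3 remedy, aid and total-cost thresholds to the convention that the data support: remedies and aids including out-of-pocket spending, other items net.

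The cost is one extra item from the insurer that already supplies the data, some revised wording, and a cost result less favourable to AGR.

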### Matching and statistical analyses

To balance the distribution of potential confounders among cases and controls we will conduct a propensity score matching using a many-to-one matching [16]. Variables for the estimation of the propensity score will be selected based on their expected importance to predict AGR participation as well as the outcomes of interest.

We will perform a two-step matching process. In the first step, for all patients who received AGR in a determined billing period, we plan to match controls with similar morbidity and cost characteristics during a.) the four billing periods prior to the index period in which the intervention took place, and b.) by additionally including the index period in the matching. This first step allows for the definition of an index period in controls. Using variables during the index billing period is complicated by the fact that no information on the temporal sequence of events within a billing period is available due to legally obliged data protection agreements. However, ignoring the index period may lead to a systematic ignorance of events leading to AGR which might have taken place in the index period. Therefore results from both analysis scenarios (a., b.) will be systematically compared. The first-step will be conducted as an exact match (pre matching) on selected variables listed in Table 6. These variables were selected due to their high expected conceptual importance for the estimation of treatment effects. Should no adequate numbers of controls be found, a more lenient matching may be employed. Controls will be drawn with repetition across billing periods. We plan to match up to 100 controls per case at this stage.

**Table 6 Tab6:** Matching criteria

Matching Criterion	Pre Matching	Propensity Score
Age	x ± 2 years	x
Sex	x	x
Area of residence		x
Days being insured		x
Level of nursing care	x	x
Hospital admission yes/no	x	x
Charlson Comorbidity index (CCI)		x
Days spent in the hospital		x
Hospital costs without out-of-pocket spending	x	x
Ambulatory costs		x
Costs of remedy		x
Costs of medical aid		x
Drug costs without out-of-pocket spending	x	x
Total costs with out-of-pocket spending		x
Main diagnoses before AGR		
*Musculo*-*skeletal*	x ^a^	
Status post fracture or joint replacement		
Cox- or gonarthrosis with endoprothesis		x
Other fractures and injuries		x
Other arthropaties		x
Osteoporosis		x
Spondylopathies and Discopathies, possibly with laminectomy		x
*Infection*		
Pneumonia and other lung inflammations	x ^a^	x
*Cardio*-*vascular system*		
Heart failure		
Chronic obstructive pulmonary disease (COPD)		x
Arterial obstructive disease with amputation or other surgery	x ^a^	x
Coronary heart diseases with surgery		x
Stroke and other cerebrovascular diseases		x
*Neuro*-*psychiatric*		
Delirium and other organic brain psychosis		x
Secondary Parkinsonsyndrom	x ^a^	x
Symptoms, effecting the nervous system and musculoskeletal system		x
Charlson Comorbidity Index		
Any Malignancy	x	x
Cerebrovascular disease		x
Chronic pulmonary disease		x
Congestive heart failure		x
Metastatic solid tumor	x	
Dementia	x	x
Hemiplegia or paraplegia		x
Mild liver disease		x
Myocardial infarction		x
Renal disease		x
Peripheral vascular disease		x
Geriatric Multimorbidity		
Cognitive deficit		x
Chronic pain		x
Depression, Anxiety		x
Incontinence		x
Severe visual/hearing impairment		x
Paraesthesia		x
Immobility	x	x
Chemotherapy	x	x

^a^At least one diagnosis from each main diagnosis group will be used to match controls. Diagnoses are allowed to differ between cases and controls within the main diagnoses group

Subsequently, propensity scores will be calculated using a logistic regression model using coded morbidity and costs under the scenarios a.) and b.), based on all variables listed in Table 6, taking statistical interactions and nonlinear associations into account. Up to four controls may be assigned to one case without repetition.

Appropriate regression models (e.g. time-event models, mixed models, two-part models) will be applied to study effects on our primary and secondary outcomes. Because treatment might also affect censoring due to mortality, competing risks models (using the Fine-Gray approach) will be applied [17]. Patients dying during the follow-up period will not be excluded from the analyses.

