## Background

Many elderly will experience a reduction in physical function, leading to more falls and injuries. This leads to a loss of independence, hospitalisation, long-term nursing home care as well as premature death [1, 2]. In 2013, 2.63 million people in Germany were in need of nursing care. Roughly two third of them received ambulatory nursing care and one third received care in a nursing home. From the years 2011 to 2013, people receiving nursing care increased by 5% [3]. In 2014, 27% of the population aged 65–79 received either ambulatory or institutionalised nursing care [4]. Given the projected demographic changes in Germany, the population in the age group ≥65 years will increase from 21% (17.3 million) in the year 2015 to 27% (21.8 million) in the year 2030 [5]. Long term nursing care and institutionalisation in a nursing home can be associated with a significant reduction of quality of life, mainly due to loss of autonomy and social contacts [6]. The increased need of long term nursing care poses a major economic challenge [7]. Thus measures to prevent, minimise or delay long term nursing care for elderly are urgently needed.

Germany has mandatory nursing care insurance attached to statutory health insurance since 1995. Elderly with disabilities or dementia can apply for a nursing care level [*Pflegestufe*]. To identify elderly in need, a basic geriatric assessment performed in general practice was introduced in 2005 [8]. Although elderly are entitled to rehabilitative services as codified in the Book V (SGB V) and XI (SGB XI) of the German social code general practitioners have only limited access to specialised rehabilitative services for geriatric patients. While the number of hospitals providing geriatric services is increasing, the demand for ambulatory services is not met [9]. Elderly patients with a need for rehabilitation prefer to stay close to their home and relatives, maintaining their everyday life [10]. Consequently, ambulatory rehabilitation is preferred. Rehabilitative services were and are still mainly available after hospitalisation e.g. for stroke or fracture after a fall.

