### Description of the AGR intervention and the setting

AGR is a multimodal intervention consisting of physiotherapy, ergotherapy, speech therapy, occupational therapy, social support by qualified social workers, psychological counselling and counselling regarding aids and care. Patients who are deemed suitable for AGR by their general practitioners can be referred to special rehabilitation centre for a geriatric assessment. If they fulfil eligibility criteria for AGR and agree to participate they receive the intervention. The intervention is tailored to the patients’ needs and delivered in individual and group sessions. Patients are commonly treated for a total of 20 days with two to three 30 min therapy units per day. Included are meals and a pick up and return service for the elderly every day. During the intervention period AGR was available in three locations in Mecklenburg-Vorpommern (Trassenheide, Ueckermünde, Waren) (Fig. 1).

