## Discussion

AGR is currently only available in few areas for elderly people from selected statutory health insurances which opted to offer AGR to their beneficiaries. Evaluation of this intervention was previously limited to uncontrolled study designs [12]. To the best of our knowledge, this will be the first study to evaluate AGR using a quasi-experimental design. This study may provide an estimation of the effectiveness of AGR on progression to higher nursing care levels and hospitalisation and other endpoints of clinical relevance. Our results will be important for providers of AGR, policy makers and stakeholders to make informed decisions on whether to continue, modify or even expand AGR to other areas in Germany. Additionally, our results might help to optimise AGR by identifying subgroups of patients who are more likely to benefit from AGR.

A limitation will be the restriction to claims data. Clinical measurements from instruments used for the geriatric assessment are not available for the control group. This might impair the quality of the matching as potential imbalance between clinical data and individual motivation to participate in AGR cannot be ruled out even if a high balance on claims data is achieved. Therefore, residual confounding may still be an issue after our matching. Final decisions on the applied methods need to account for the precise properties of the data.

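### Table 6 uses ambulatory service billing only as a cost total, so a billed GP geriatric assessment, a plausible marker of need and referral, is left out of the propensity score

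*Protocol article*

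**What the plan says.** Under Matching and statistical analyses, variables for the score are "selected based on their expected importance to predict AGR participation as well as the outcomes of interest". The same section ties the score to coded morbidity and costs and to the variables in Table 6. Table 6 has one row taken from ambulatory service billing, ambulatory costs, which enters the score but not the pre-matching. No row is a billed service item.

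Study design lists among the supplied data "billing data for ambulatory services (EBM position numbers", that is, service-level codes. Outcome measures and data collection adds: "All variables are provided for each billing period during the observation period". Cases and controls are both AOK Nordost members, and one data supply is described for the study.

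On the route into AGR, Background says: "To identify elderly in need, a basic geriatric assessment performed in general practice was introduced in 2005". Description of the AGR intervention and the setting says: "Patients who are deemed suitable for AGR by their general practitioners can be referred to special rehabilitation centre for a geriatric assessment".

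The Discussion acknowledges that "Clinical measurements from instruments used for the geriatric assessment are not available for the control group" and that residual confounding may remain. It does not mention billing codes as a partial substitute.

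**The concern.** AGR starts with a GP's judgement that a patient is suitable. A record that the GP had looked into geriatric need is likely to be more common among AGR patients than among controls of similar cost and coded morbidity. It is also likely to go with higher risk of nursing care progression, nursing home admission and fracture, because the assessment exists to find people in need. A cost total does not show what was billed, so two patients with equal ambulatory costs can differ on this marker.

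If the marker stays unbalanced, all three primary comparisons carry some confounding by indication. In this mechanism the AGR group has the greater need, so the bias runs against AGR and could hide a benefit.

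**Working it through.** **1. The plan's own figure.** About 700 AGR patients with up to four controls each gives 700 × 4 = 2800, which agrees with the Sample size section. Adding score variables does not change these targets.

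**2. What Table 6 already covers.**
- In both the pre-matching and the score: nursing care level (defined in Table 4 by hours of daily help), immobility and dementia.
- In the score only: costs of remedies and of medical aids, hemiplegia, incontinence, cognitive deficit, visual or hearing impairment, stroke, osteoporosis, other fractures and injuries.
- Not covered: any billed ambulatory service. Frailty (R54), an AGR criterion in Table 1, also has no row.

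The proxies are real but coarse. Level 1 requires at least 1.5 hours of daily help, and Table 3 excludes levels above 2, so people below level 1 can differ considerably in function.

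**3. Illustrative size.** The article gives no frequency for the GP assessment in either group and no associated risk, so every input here is an assumption: prevalence p1 = 50-60% in AGR patients, p0 = 20% in controls, outcome risk ratio RR = 1.3-2.0. For a binary unadjusted confounder the observed risk ratio is multiplied by

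[1 + p1(RR − 1)] / [1 + p0(RR − 1)]

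| RR | p1 | p0 | Factor | A true 0.80 appears as |
|---|---|---|---|---|
| 1.3 | 50% | 20% | 1.15/1.06 = 1.085 | 0.87 |
| 1.3 | 60% | 20% | 1.18/1.06 = 1.113 | 0.89 |
| 2.0 | 50% | 20% | 1.50/1.20 = 1.25 | 1.00 |
| 2.0 | 60% | 20% | 1.60/1.20 = 1.333 | 1.07 |

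The range is about 1.09-1.33. It treats the marker as unrelated to everything already matched. To the extent that the existing proxies carry the same information, the remaining bias is smaller. With 50% against 45% and RR 1.5, for example, the factor is 1.25/1.225 = 1.02.

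**4. Scale against detectable effects.** The article gives no power calculation. Assuming two-sided 5%, 80% power and 700 against 2800 unpaired, the smallest detectable risk ratio is about 0.67 at a control risk of 10%, 0.77 at 20% and 0.82 at 30%. Multiplying 0.77 by 1.333 gives 1.03, so the upper end could mask an effect of detectable size. Multiplying it by 1.02 gives 0.79, so the lower end is minor.

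**5. Direction.** AGR is closed to people whose health is too poor to take part (Eligibility criteria for AGR). The exclusions applied to controls (Table 3) remove nursing home residents, care levels above 2 and very high costs, but have no direct counterpart to inability to attend. Controls of that kind would have worse outcomes and would favour AGR. The two mechanisms oppose each other, and the article does not allow them to be netted.

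**The case against.** The strongest reply is that Table 6 already contains many markers of function and that the Discussion openly concedes residual confounding. This stands. A reader might infer that functional need is left wholly uncontrolled. Three of its markers are both pre-matched and in the score, so that reading fails.

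A second reply is that the link from GP assessment to referral is not in the article. This also stands. The GP assessment appears only as background, and the assessment that decides eligibility is done at the rehabilitation centre. A reader might take the GP assessment to be a required step into AGR, but the text says only that GPs judge suitability and refer. The link is a plausible inference.

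Third, a billed item shows that an assessment took place, not what it found, and may partly reflect practice style. That limits what it can achieve. But its stated purpose is to identify people in need, so there is reason to expect a relation to outcome as well as to referral.

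Fourth, it may be said that the selection rule is not broken. Agreed: the rule speaks of expected importance and does not promise every available predictor. The item fits the rule's aim, and its omission is a missed opportunity, not a contradiction. Likewise, the Discussion calls the restriction to claims data a limitation, not the main one.

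What remains after these replies is that service-level data said to be supplied go unused in an explicit covariate list. Conceding residual confounding does not reduce it.

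**Conclusion.** The point holds as a likely source of residual confounding by functional need and referral that could be reduced cheaply. Table 6 does not use the supplied ambulatory service codes except through cost, and a GP geriatric assessment is a plausible predictor of both participation and the primary outcomes.

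The size is not known. The factor of about 1.09-1.33 rests entirely on assumed prevalences and risk ratios and takes no account of the existing proxies. The net direction is also open. The documents support neither a claim that the primary results will be invalid nor a claim that they will be biased in a particular direction. The conclusion further assumes that the assessment can be identified from the supplied EBM numbers; the article says only that such numbers are supplied.

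**What to change.** If the supplied EBM numbers identify it, add to the propensity score rows of Table 6 a yes/no indicator of GP basic geriatric assessment in the four billing periods before the index period. Where identifiable, add home visits and the number of quarters with GP contact over the same periods. Home visits may help separate controls who could not have attended. Report the balance of these items after matching.

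Do not require them in the exact pre-matching, which already foresees a more lenient match if controls run short. Keep the limitation in the Discussion and add that a billed item shows that an assessment was done, not its result.

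The cost is a few more score variables from data already described as supplied, and possibly slightly fewer close matches, drawn from a pool of around 250,000. Restricting the items to pre-index periods avoids the unknown order of events within the index quarter, but misses a work-up that fell in that quarter. The Discussion leaves final method decisions open, so the addition does not conflict with the protocol.
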